**6.7 Study Design**

Three study designs will be used in the study. Study designs differ according to the study type.

**Qualitative study**: **FGD and in-depth interview (IDI)** methods of qualitative study will be used at baseline. The aim of this objective is to explore community perceptions of intimate partner violence during pregnancy.

**Quantitative study:** A two-arm parallel-group cluster randomized controlled trial with a 1:1 allocation ratio is designed to examine whether couple-based violence prevention education

provided by HEWs reduces intimate partner violence during pregnancy in the Hadiya Zone, Southwest Ethiopia. Clusters will be found in selected districts of Hadiya Zone.

**6.8 sample size**

**Qualitative study:** the sample size for a qualitative study will be determined by information saturation (Dworkin, 2012). But, for planning purposes, eight (8) Focus Group Discussions (FDG)( at least two FGDs from male partners (husbands of pregnant women), two FGDs from religious leaders, two FGDs from community leaders, and two FGDs from the women's development army) will be considered. Moreover, six in-depth interviews (IDI) among pregnant women and 70**participants** will be involved in FGD, and IDI will be involved in order to explore community perspectives towards IPV in pregnancy.

**Quantitative study (CRCT):** sample size is calculated by using the following parameters: The prevalence of IPV during pregnancy (p) was  37.5% in a study conducted in Tigray, Ethiopia (Adhena et al., 2020). The expected decline of IPVp following the intervention will be 20%, with 80% power, a 95% confidence interval, an intra-correlation coefficient (ICC) variation of 0.05, a loss to follow-up of 20%, and a design effect of 2.3. Hence, the sample size is based on Stata version 16.

Design Effect (DE) = 1 + ρ (m-1)

Where,

DE=Design effect,

ρ= intra-cluster correlation coefficient = 0.05

m=number of participants per cluster = 27.

DE=1+0.05(27-1) =2.3

Attrition (20%)

=216 couples per control group and 216 couples per intervention group; sample size =432 couples, making a total of 864 participants.

Total cluster (k) = 16 kebeles (clusters)

## 6.9 Sampling Procedure

We will use the multi-stage cluster sampling to select eligible couples in the study area. Four districts (Soro, Lemo, Analemo, and Duna) are selected randomly from the 13 districts in the zone, which consists of 116 rural kebeles. Distance and geographical accessibility will be considered to select interventions and control kebeles. At least one kebele will be left between the kebele included in the trial to serve as a buffer zone between the two arms in order to avoid information contamination. Out of 116 kebeles, 49 non-adjacent and accessible kebeles are identified. Finally, Out of 49, 16 rural kebeles—the lowest administrative units from the four districts—will be selected by simple random sampling technique for the intervention and control groups. In each cluster, there will be 27 pregnant women with their husbands who will participate, making 216 couples per arm (Figure 4).

16 clusters

Hadiya Zone (13 districts)

By simple random sampling

By simple random sampling

Soro, Lemo, Analemo and Duna districts (116 kebeles)

49 non-adjacent and accessible kebeles (clusters)

8 intervention clusters

8 control clusters

27 eligible couples per cluster

27 eligible couples per cluster control clusters

216 eligible couples per arm

216 eligible couples per arm

Figure 3: diagrammatic representation of sampling procedure

**Qualitative part:** we will deploy purposive sampling techniques for the FGD and IDI. Women support groups, male partners, religious leaders, and community leaders will be selected for the FGD. In-depth interviews (IDI) will be carried out among pregnant women until the information saturation

**5.10 Operational Definition**

**Couple**: a man and woman living together, whether married or not.

**Intimate partner**: a current husband or cohabiting partner (living in the same house without formal marriage)

**Intimate partner violence**: pregnant women who reported any violence in the form of physical, psychological, or sexual violence, or any combination of the three, by their husband during pregnancy (Trott et al., 2017).

**Physical violence** refers to when a pregnant woman reports one or more acts of slapping or throwing something at her that could hurt her, pushing, shoveling, or pulling her hair, hitting her with her fist or with something else that could hurt her, kicking, dragging, or beating her up, attempting to choke or burn her on purpose, and threatening to use or actually use a gun, knife, or other weapon during the most recent pregnancy (WHO, 2010).

**Sexual violence:** refers when pregnant women reports that they experience one or more physically forced her to have sexual intercourse with him when she did not want to, forced her with threats or in any other way to perform sexual acts she did not want and physically forced to perform any other sexual acts she did not want toduring the most recent pregnancy (WHO, 2010)

**Pregnancy Screening**

All women residing in the intervention and control arms will be screened using a pregnancy screening questionnaire adapted from Nega A et al. (2010, Kersa, Ethiopia. “If the answer to at least one of the six pregnancy screening questions is ‘yes’, pregnancy will be ruled out. Women who responded in a way that suggested the possibility of being pregnant will be asked to provide a urine sample for a pregnancy test, which will be done using a dipstick in the respondent’s home (Assefa et al., 2013).

Table 1: pregnancy screening questions

| S. No | Items | Yes | No |
| --- | --- | --- | --- |
| 1 | During the last four weeks, did you give birth? |  |  |
| 2 | Do you fully breastfeed or are you less than six months postpartum and have not experienced menstrual bleeding since bearing your child? |  |  |
| 3 | During the last week, did your last period begin? |  |  |
| 4 | In the last week, did you experience a miscarriage or an abortion? |  |  |
| 5 | Since your last period, have you avoided sexual intercourse? |  |  |
| 6 | Have you been consistently and appropriately using a safe method of contraception (pills, injectables, and Norplant)? |  |  |

**6.11 Recruitment of clusters or study participants**

Clusters included in the intervention and control groups will be selected from the four districts in Hadiya zone, namely Soro, Lemo, Ana Lemo, and Duna woredas. The couple violence prevention education will be done in eight intervention clusters of the four districts. Similarly, eight clusters from the four districts will be assigned to the control group.

**Requirement of the study participants (n=426 couples**)

Intervention group (n=213 couples)

Control group (n=213)

Control group (study 1)

8 clusters (kebeles)

n=213 couples (213 pregnant women+ 213 husbands)

GBVP education (study2)

8 clusters (kebeles)

N=213 couples (213 preg. Women+213 husbands)

Control group (study group 1)

- No intervention will be provided from the research team
- Health Extension workers in the clusters continue to provide HE on Health extension packages.

Violence prevention education (study group 2)

- Monthly couples (pregnant women and husbands) education sessions from 1^st^ trimester to term(delivery)
- Data collection at
- Baseline and end-line(two months after intervention)

 Intervention and determination of IPV experience, Knowledge, attitude and controlling towards IPV and wome’s autonomy and self-efficacy

**Randomization of clusters**

Figure 4: diagrammatic representation of study activities

## 6.12 Randomization

After getting permission from Kebele administrators (gatekeepers), clusters will be used for randomization into intervention and control group. Kebeles in districts will form the units of randomization for the trial. Randomizations of the clusters will be performed before recruiting the participants into the two arms. All kebeles found in four districts will be listed. Each cluster will be given an individual code and an alphabetical list. A statistician who is blind to the study groups will perform the randomization. The statistician will assign the 16 clusters into 8 intervention and 8 control arms by applying permuted block randomization methods. Randomization into two study groups will be based on a 1:1 ratio.There will be adequate buffer zone to avoid information contamination

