## 6.13 Blinding

Neither the Health extension workers nor the participants will be informed about the intervention hypothesis

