**Consort Diagram**

The study protocol containing the detailed information is depicted in the consort diagram below (Figure 5).

116 rural kebeles found in Soro,Lemo, Analemo and Duna Districs

49 eligible kebeles

16 kebeles selected

Randomization of 16 kebeles (intervention and control arms)

Allocation

Intervention arm (8 clusters)

Control arm (8 clusters)

Participants will be assessed for eligibility criteria

 Participants will be assessed for eligibility criteria

Enrollment

Informed consent and

Baseline data collection

Informed consent and

Baseline data collection

Intervention group receive

CBVPE

Control group continue to receive routine care

Analysis

8 months follow-up survey

Intervention

Identification of couples whose wife is pregnant

Figure 5: Consort flow diagram

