**6.25 Timeline of the study**

Both primary and secondary outcomes will be assessed as illustrated participants’ timeline of enrolment, implementation and assessment schedule (Table 3)

Table 3:Participants’ timeline of enrolment, implementation and assessment schedule

| Activity | Study period | | | | | | | | | |
| --- | --- | --- | --- | --- | --- | --- | --- | --- | --- | --- |
|  | Enrolment | Allocation | Intervention | | | | | | | Close-out |
|  | Month 1 | Month 2 | Months | | | | | | | Month 11 |
|  |  |  | 3 | 4 | 5 | 6 | 7 | 8 | 9 |  |
| Enrolment |  |  |  |  |  |  |  |  |  |  |
| Eligibility screen |  |  |  |  |  |  |  |  |  |  |
| Informed consent |  |  |  |  |  |  |  |  |  |  |
| Allocation |  |  |  |  |  |  |  |  |  |  |
| Baseline assessments |  |  |  |  |  |  |  |  |  |  |
| Interventions |  |  |  |  |  |  |  |  |  |  |
| Endline assessments |  |  |  |  |  |  |  |  |  |  |

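### Kebeles are randomised before couples consent and are measured, Table 3 gives a different order, and no section conceals allocation from recruiters, interviewers or couples

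*Protocol*

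**What the plan says.** **Order of steps.** Protocol section 6.12 states: "Randomizations of the clusters will be performed before recruiting the participants into the two arms". Figure 5 (Consort Diagram) agrees. It has a box reading "Randomization of 16 kebeles (intervention and control arms", followed by separate boxes for each arm in which "Participants will be assessed for eligibility criteria", then consent and baseline data collection. The Pregnancy Screening section also speaks as if arms already exist: "All women residing in the intervention and control arms will be screened using a pregnancy screening questionnaire".

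Table 3 (section 6.25) differs. Its column heads run "Enrolment | Allocation | Intervention" with "Month 1 | Month 2 | Months" beneath, so enrolment is month 1 and allocation is month 2. Its rows run enrolment, eligibility screen, informed consent, allocation, baseline assessments.

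**Safeguards.** Section 6.13 says: "Neither the Health extension workers nor the participants will be informed about the intervention hypothesis". Section 6.15.2 repeats this. Section 6.12 adds: "A statistician who is blind to the study groups will perform the randomization".

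**Who does the work.** Section 6.18 has ten nurses collecting the quantitative data and gives the supervisors oversight of both health educators and data collectors. The work plan (section 7, Table 4) lists educators, alongside data collectors, against baseline data collection. Section 6.15 says the education is delivered by eight health extension workers who work in the intervention kebeles.

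**The concern.** In a cluster trial, randomisation balances the kebeles. It balances the couples only if who enters, and what they report at entry, does not depend on the arm. Randomising clusters first is acceptable when recruiters and couples do not know the allocation. The protocol never says that they will not.

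Two steps are exposed:

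- **Consent and eligibility.** Section 6.5 requires couples to be willing to be visited at home. In intervention kebeles, section 6.15.3 adds monthly dispute screening and absence visits by the educators, and couples are asked to attend six sessions. Section 6.15.1 gives control couples only the usual services. If couples know the arm, the same criterion carries a different burden in each.
- **Baseline measurement.** Baseline violence is self-reported. If it is given or recorded with allocation known, the variable that would be used to check or adjust for imbalance may itself differ by arm.

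The primary outcome is violence reported by the woman, so selection related to violence acts directly on the main comparison.

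**Working it through.** **1. Orders side by side**

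| Place | Consent relative to allocation | Baseline relative to allocation |
|---|---|---|
| Section 6.12 | after | after (baseline follows recruitment) |
| Figure 5 | after | after |
| Table 3 (columns, months, row sequence) | before | after |

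Section 6.12 and Figure 5 contradict Table 3 on consent. None of the three puts baseline before allocation. The cell marks of Table 3 and the layout of Figure 5 are not visible in the available text. Table 3 is therefore read from its heads and rows, and the place of Figure 5's box on identifying pregnant couples cannot be determined.

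**2. What each safeguard covers**

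- Withholding the hypothesis does not withhold the arm.
- A blind statistician protects the sequence, not recruitment after it is released.
- Screening all women protects the finding of pregnancies, not eligibility judgement, consent or baseline answers.

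**3. The plan's effect size, needed for scale**

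Section 6.8 gives prevalence 37.5%, a 20% decline, 80% power, 95% confidence, design effect 1 + 0.05(27 − 1) = 2.3 and 20% loss. Reading the decline as 20 points (37.5% to 17.5%), the usual two-sided formula without continuity correction gives 78 per arm. Then 78 × 2.3 = 179.4, rounded up to 180, and 180 × 1.2 = 216, which is the stated figure. A relative 20% decline (to 30%) would need 623 × 2.3, or 1,433 rounded up, and × 1.2 about 1,720 per arm. The plan therefore rests on 20 points.

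**4. Illustration of differential consent**

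Assume no true effect, prevalence 37.5% in both arms, and differential refusal in intervention kebeles only. A fraction *a* of violent couples and *b* of non-violent couples decline. The documents give neither *a* nor *b*.

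Enrolled prevalence = 0.375(1 − a) / [0.375(1 − a) + 0.625(1 − b)]

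| a | b | Calculation | Enrolled prevalence | Difference from 37.5% |
|---|---|---|---|---|
| 0.15 | 0.05 | 0.31875 / 0.9125 | 34.9% | 2.6 points lower |
| 0.20 | 0.05 | 0.3000 / 0.89375 | 33.6% | 3.9 points lower |
| 0.25 | 0.05 | 0.28125 / 0.875 | 32.1% | 5.4 points lower |
| 0.05 | 0.05 | 0.35625 / 0.9500 | 37.5% | none |
| 0.05 | 0.15 | 0.35625 / 0.8875 | 40.1% | 2.6 points higher |

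The first three rows amount to 13–27% of the planned 20 points (2.6/20 and 5.4/20). The last two show that equal refusal gives no bias and that the reverse pattern would hide a benefit.

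**5. Effect on an unadjusted test**

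Effective number per arm = 216 × 0.8 / 2.3 = 75.1. Standard error = √(2 × 0.375 × 0.625 / 75.1) = 7.9 points. A shift of 2.6–5.4 points is 0.33–0.68 standard errors, so a nominal 5% two-sided test would reject about 6–10% of the time.

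**The case against.** **The direction is unknown.** Nothing in the documents shows that violent husbands would decline more often. Abused women might press to join, or violent control husbands might refuse home visits. This stands. A reader might infer a predictable false benefit, but the documents support only that bias is possible.

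**Table 3 is not a ready-made answer.** A reader might infer that adopting Table 3 solves the problem. It does not: its rows list baseline after allocation, so it protects eligibility and consent but not baseline measurement.

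**Staff knowledge of allocation is inferred.** No section says that recruiters know the arm, and separate nurses are recruited to collect data. This stands in part. The finding is that concealment is not stated. The work plan's listing of educators at baseline, and supervisors shared between education and data collection, make knowledge of the arm likely but do not prove it. The consent forms are not in the available material, so whether their wording differs by arm cannot be judged.

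**The analysis would absorb some of it.** The section on data processing and analysis compares prior exposure to violence between arms and fits a longitudinal GEE. That would offset part of a stable, recorded baseline difference. It would not correct for unmeasured traits, or for baseline answers that are themselves affected by knowing the arm. The 2.6–5.4 points are a difference in enrolled prevalence, not a forecast of the adjusted endline result. To say that randomisation is undone would overstate it.

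**Holding all allocation until the last interview could break the schedule.** The Summary allows a month for baseline, sections 6.15.1 and 6.15.2 put baseline at 10–12 weeks and the start of sessions at 13–16 weeks, and section 6.19 gives educators three days' training. A couple interviewed at 12 weeks at the start of that month would be at about 16 weeks by its end, before training begins. This stands and shapes the fix.

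**Conclusion.** The point holds as one of order and concealment. Section 6.12 and Figure 5 contradict Table 3 on whether consent precedes allocation. All three leave baseline after allocation, and no section keeps the allocation from recruiters, interviewers or couples. Differential consent and differential baseline reporting by arm are therefore possible under the plan as written.

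The size is not known. The 2.6–5.4 points rest on assumed refusal rates in one arm, no true effect and no adjustment, with zero or the opposite sign equally compatible with the documents. The contradiction and the missing concealment can be read directly from the text. The direction and amount of bias cannot. Correction is warranted because analysis can repair this kind of selection only in part, while the order of steps can prevent it. The sample size is unaffected.

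**What to change.** Reconcile section 6.12, Figure 5 and Table 3 to one order: screening, consent and baseline in a kebele are completed before its allocation is disclosed to field staff, health extension workers and couples.

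- The statistician may generate the list earlier but keeps it concealed, and releases it by kebele or block once baseline there is complete. This lets the stated session 1 window be kept. If release is by block, wait until baseline is finished in every kebele of the block, so that one disclosure does not reveal another's arm.
- In Table 3, move the baseline row above allocation.
- Keep educators out of recruitment and baseline interviewing, and correct the work plan entry. State in section 6.13 who is unaware of allocation at consent and at baseline.
- Report numbers eligible, approached and refusing by kebele, so that differential consent can be seen.

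**Cost.** No added visits or participants. Section 6.14 already bases the education on baseline findings, so baseline has to come before the intervention in any case. The small downside is that intervention educators are named and given their three-day training in a short window after baseline.

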## 6.13 Blinding

Neither the Health extension workers nor the participants will be informed about the intervention hypothesis

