**6.15 Description of the Intervention**

The purpose of the study is to provide community-based health education to couples on violence prevention to reduce intimate partner violence during pregnancy. A group health education on violence prevention, including intimate partner violence, for couples in the intervention group will be provided in a place center for the participants. 16 kebels found in the four districts will be the study clusters.

A package of health education messages on violence prevention will be provided to couples living in the intervention arm. The package was adapted from a psychosocial education study conducted among couples (Mutisya et al., 2018) and gender transpormative education on intimate partner violence in Tanzania (Harvey et al., 2021). The health education messages will be conducted by health extension workers who are working in intervention clusters (kebeles). Eight health extension workers will be selected for the intervention (CBVP education). The following criteria will be used to recruit health extension workers:

- Health Extension Workers who are female
- able to speak Amharic and the local language (Hadiyisa).
- willing to participate in the study period
- Good interpersonal and communication skills
- Having participated in a survey previously

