**6.15.2 Description of education sessions**

**Control group (study group 1):** participants in the control clusters receive routine standard care from the health extension workers**.** Education on violence prevention, including intimate partner violence, will not be provided by the research team. This group will simply receive the health extension package services provided by HEWs.

**Intervention group (study group 2)**: Pregnant women and their husbands will receive couple-based violence prevention education (CBVPE) from the 13–16 weeks of gestation to delivery for six months. The intervention package is aimed at raising knowledge and awareness of gender-based violence, types of intimate partner violence, adverse maternal and new-born outcomes of IPV during pregnancy, common triggers of intimate partner violence during pregnancy and its management, a healthy relationship in marriage, communication, and problem-solving skills. After adequate training, HEWs will provide health education to couples in the intervention arms at the health post in groups. It will be provided every month for six consecutive times. Each session may take 50-60 minutes. All sessions will contain interactive lectures, take-home exercises, and reflection. During class sessions, flip chart paper and posters will be used. It is designed with the intention that they will be carried out in an enclosed workshop space. Neither the HEWs nor the participants will be informed about the intervention hypothesis.

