**6.24 Ethical Consideration**

Ethical approval of the study will be obtained from the Ethical Review Board of Jimma University. Then, permission letter to precede the study will be obtained Regional health Bureau and Zonal Health department. The research participants will be enrolled into the study after informed verbal and written consent is obtained. Confidentiality of the respondents will also be maintained. The purpose of the study and the right of the respondent not to participate and not to answer the question for which she didn't want to will be explained carefully to respondents before asking informed and written consent to conduct interview. All interviews will be taken place privately at place and time chosen by the respondent. Strict confidentiality will be assured through anonymous recording and coding of questionnaire and placing it in a safe place after they have been collected. For qualitative study, the interview will be carried out in a private place for the purpose of concentration and privacy of participants. Permission to use a tape recorder will be obtained from the participants prior to the interview for all qualitative study participants.

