**Appendix-iv: CBVP-Education manual to trainers**

**Introduction**

Couples education package is a set of preventive messages designed to help foster a process of change to reduce intimate partner violence during pregnancy amongst couples in Hadiya Zone, Southwest, and Ethiopia. The contents included in the education manual to prevent intimate partner violence in pregnancy includes the following

- Gender-based violence
- Violence against women
- Intimate partner violence
- Types of intimate partner violence (physical, sexual, and psychological or emotional violence)
- Magnitude of intimate partner violence in pregnancy
- Inequitable gender norms and consequences
- The relationship between intimate partner violence and power and control
- Common triggers of IPV in pregnancy
- Uhhealthy and healthy relationship
- Common triggers of IPV and ways to challenge the triggers
- Effective communication and conflict resolution in relationship

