**The training manual objective**

1. To enable the participants describe the GBV, VAW, IPV, IPV, types of IPV and Magnitude of IPV
2. To enable the couples to describe the extent of intimate partner violence
3. To enable the couples to explain adverse consequences of intimate partner violence during pregnancy
4. To enable couples to describe common triggers of violence and state the common ways to challenge the triggers of IPV
5. To enable the couples to describe inequitable gender norms related to IPV during pregnancy
6. To enable the couples to describe an effective communication skills and nonviolent ways of conflict resolution

The CBVPE session schedules, titles and objectives

| Session schedule by Gestational ages | Session title | Session objectives |
| --- | --- | --- |
| 1^st^ session  (13-16 weeks) | Program introduction & understanding GBV, VAW and IPV | To describe the goal of the program  To define GBV, VAW and IPV  To explain types and magnitude of IPV |
| 2^nd^ session  (17-20 weeks) | Consequences and common triggers of IPV during pregnancy | To describe adverse maternal and new-born consequences of IPV during pregnancy  To explain economic and social consequences of IPV during pregnancy  To identify common triggers of IPV  To state the ways to challenge triggers of IPV |
| 3^rd^ session  (21-24 weeks) | Inequitable gender norms related to IPV during pregnancy | To describe common gender norms for women and men  To differentiate gender and sex  To understand how inequality gender norms contribute to IPV during pregnancy  To describe the ways to challenge and transform inequitable gender norms |
| 4^th^ session  (25-28 weeks) | Unhealthy and healthy relationship | To differentiate healthy and unhealthy behaviors in marital relationship  To state important characteristics of healthy relationships |
| 5^th^ session  (29-32 weeks) | Power and control in relationship &  Joint decision making | To define power and control  To describe healthy power balance within relationship  To explain benefits of joint decision making  To describe and apply seven strategies to joint decision making |
| 6^th^ session  (33-36 weeks) | Communication & conflict resolution | To describe effective communication skills in relationship  To explain nonviolent ways of conflict resolution in relationship |

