**Physical intimate partner violence (IPPV) includes**

- Slap you or throw something that could hurt the partner
- Push the partner,
- Punch in abdomen
- Kick in abdomen
- shove the partner or pull the hair of the partner,
- Hit with his fist or with something else that could hurt the partner
- Kick ,
- Drag about or beat the partner up
- Attempt to choke or burn on purpose
- Threaten to use or actually use a gun, knife or other weapon against the partner

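### The protocol says educators and participants will not be told the hypothesis, but its own manual and handouts show the intervention arm the expected direction, leaving the self-reported primary outcome open to differential reporting.

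*Protocol*

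**What the plan says.** Section 6.13 (Blinding) consists of one sentence: "Neither the Health extension workers nor the participants will be informed about the intervention hypothesis". Section 6.15.2 repeats it at the end of the description of the intervention sessions: "Neither the HEWs nor the participants will be informed about the intervention hypothesis". Section 6.12 adds only that the statistician who randomises is blind to the study groups.

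Other parts of the protocol disclose the aim:
- The introduction to the trainers' manual (Appendix iv) calls the package "a set of preventive messages designed to help foster a process of change to reduce intimate partner violence during pregnancy amongst couples".
- The manual's session table gives as the first objective of session 1: "To describe the goal of the program".
- Section 6.15 gives the purpose of the study as to "provide community-based health education to couples on violence prevention to reduce intimate partner violence during pregnancy".
- Section 6.24 (Ethical Consideration) says of consent: "The purpose of the study and the right of the respondent not to participate and not to answer the question" and, later in the same sentence, "will be explained carefully to respondents before asking informed and written consent to conduct interview".
- The Annex V handout names the acts that count as violence, for example: "Threaten to use or actually use a gun, knife or other weapon against the partner".

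The primary outcome (sections 5.10, 6.6.1 and 6.17) is a yes/no variable built from what the woman reports to an interviewer.

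**The concern.** Withholding the hypothesis is meant to stop respondents from shaping their answers to the result the study hopes for. The hypothesis in section 5.2 is that violence is lower with the education than with usual care. An educator whose manual says the package exists to reduce violence, and a couple who attend six sessions on that theme, know the hoped-for direction without hearing the formal statement.

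This matters because the outcome is self-reported and the teaching reaches one arm only. Women in that arm may report less, from loyalty to the programme or to a husband who attended with them. The session 3 handout also lists arrest and imprisonment among the consequences for perpetrators, a plausible reason to conceal. They may instead report more, having learned to recognise certain acts as violence. Either would move the arm difference with no change in behaviour. If the report relies on 6.13 as written, a change in reporting could be presented as a change in violence.

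**Working it through.** **1. Who learns what, by arm.**
- Intervention educators: the manual's first sentence states the intended effect. This conflicts directly with 6.13 and 6.15.2.
- Intervention couples: the programme's goal is a session 1 objective in the schedule table, and the session 1 script announces gender-based and partner violence as the topic. The expected direction is evident.
- Control educators: no passage tells them the aim or the hypothesis.
- Control couples: their only route is the explanation of purpose at consent, which is described the same way for both arms.

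Knowledge of the direction therefore differs by arm.

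**2. Overlap of teaching and outcome items** (Annex V handout against items 801 to 803 of the women's questionnaire).
- Physical: 6 of 6 acts covered.
- Sexual: 3 of 3.
- Psychological: 3 of 4; the item on scaring or intimidating on purpose is absent.
- Total: 6 + 3 + 3 = 12 of 13, mostly in nearly the same words.

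**3. Size, as an illustration.** The point rests on no figure in the plan. For context, the planned 216 couples per arm reproduces from 37.5% against 17.5% (a 20-point fall), two-sided 5%, 80% power: 78 per arm; × 2.3 = 179.4, rounded to 180; × 1.2 = 216.

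Let π be the true prevalence, the same in both arms, and d the share of affected women who disclose.

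Spurious difference = π × (d_control − d_intervention)

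Take π = 37.5% (section 6.8, itself a survey figure, used here as if true).
- Under-reporting: d_control = 1 and d_intervention = 0.9 give 37.5% against 37.5 × 0.9 = 33.75%, a false benefit of 3.75 points. That is 3.75 / 20 = 0.19, or about a fifth of the planned fall.
- Better recognition: d_control = 0.9 and d_intervention = 1 give 33.75% against 37.5%, a false harm of the same 3.75 points.

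The chance of a significant false benefit, by normal approximation with an effective size of 216 / 2.3 = 93.9 per arm, is about 8%, 19% and 38% when 10%, 20% and 30% of affected intervention women conceal. With no reporting difference it would be about 2.5%, the benefit side of a two-sided 5% test. All these shares are assumptions; the protocol supplies none.

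**The case against.** The strongest reply is that the protocol promises only that the hypothesis will not be told. The hypothesis is comparative, and knowing that a programme aims to reduce violence is not the same as knowing that reports will be compared between arms. That is literally true. The goal still gives away the direction, which is what affects reporting.

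Several safeguards count in the plan's favour. Outcome data are collected by female nurses, a role separate from the educators, chosen to encourage disclosure (6.18). Interviews are private, at a place and time the respondent chooses, with anonymous coding (6.24). Both arms answer the same questionnaire at baseline before any session (6.21), so control women also hear the acts named. These measures support disclosure in both arms, but they do not remove motives or recognition acquired only through the sessions.

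A reader might infer that consent itself reveals the hypothesis. The documents do not support that. The consent wording is not available, section 6.15 is not a consent script, and consent is described identically for both arms. A reader might also infer that session 1 will certainly teach the goal. It is an objective in the schedule table, but the detailed session 1 plan does not list it.

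Finally, unmasked participants are unavoidable in couple education. That stands: the fault is the statement, not the absence of blinding.

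**Conclusion.** The point holds in this form: the non-disclosure statement cannot be true of intervention educators, and it gives little cover for intervention couples, who are taught the direction and nearly all the outcome acts. The primary outcome is therefore open to differential under- or over-reporting, and the direction of any bias is unknown.

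It would go too far to say that the outcome has no protection, since private interviews by separate female nurses do help. It would also go too far to say that reporting bias could explain effects of the size cited in the literature review. With no true effect, a concealment share of c gives a relative reduction of c by construction, so matching the cited reductions shows nothing. The 3.75 points per 10% of affected women is a scale for judging the problem. It assumes 37.5% true prevalence in both arms and full disclosure among controls.

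**What to change.** 1. In 6.13 and 6.15.2, state that health extension workers and couples in the intervention clusters are not masked to the intervention or its aim. Non-disclosure of the hypothesis may be kept for control health extension workers. Reconcile both sections with the consent paragraph in 6.24, the manual's introduction and the session 1 objectives.
2. Leave the consent content intact. Intervention couples must hear about the sessions they are agreeing to, so hiding the programme at consent is not the remedy. Instead, script one identical, neutral introduction to the baseline and endline interviews in both arms, with no mention of the programme.
3. State the primary conclusion as reported intimate partner violence, in line with the operational definition in 5.10.
4. Add a sensitivity table, here or in the analysis plan, showing how much differential under-reporting in the intervention arm would remove the observed effect, and how much over-reporting would mask one.

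The cost is a few sentences, one interview script and one table. The downside is a more cautious claim.
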